### The Beck depression inventory

3.4

The Beck Depression Inventory (BDI) is one of the most widely used measures in both research and clinical practice for assessing depression. BDI is a 21-item, self-report rating inventory that measures characteristic attitudes and symptoms according to diagnostic criteria listed in the Diagnostic and Statistical Manual for Mental Disorders. BDI demonstrates high internal consistency, with alpha coefficients of 0.86 and 0.81 for psychiatric and non-psychiatric populations, respectively (56).

### The affective lability scale 18

3.5

The Affective Lability Scale 18 (ALS-18) is a valid and reliable instrument for measuring affect lability. ALS measures individual proneness to rapid shifts from the different emotional states of anxiety, depression, anger, and hypomania (57). The ALS-18 item version is based on a three-factor model of affective lability (anxiety/depression, depression/elation, and anger), with each factor retaining at least two items from each of the original six subscale versions. ALS-18 is highly correlated with the original 54-item version (*r* = 0.94).

## Assessment of cognitive function

4

Cognitive functioning at baseline (T0) and post-intervention (week 14, [T3]) will be assessed using the Cambridge Neuropsychological Test Automated Battery (CANTAB). CANTAB measures are a reliable, valid, sensitive way of collecting comprehensive and accurate information on cognitive functioning in a clinical sample (58). Test batteries are delivered digitally using an iPad, allowing for standardized data collection at multiple time points and automated creation of comprehensive data sets. The level of information provided by each CANTAB measure allows for in-depth analysis of highly specific components of cognitive functioning providing specific insight into intervention efficacy within the context of a much wider dataset (59, 60). A customized test battery, consisting of 7 separate neuropsychological assessments (Table 4) was designed for data collection during this clinical trial.

**Table 4 tab4:** CANTAB neuropsychological test aspects.

Neuropsychological test (CANTAB)	Test variation	Administration time (Min)	Outcome measures
Motor Screening Task (MOT)	Voice	2	Accuracy Difficult/speed adjustment
Spatial Working Memory (SWM)	Recommend Standard Tone 2.0	4–6	Errors Incorrect selection, reselection
Emotional Recognition Task (ERT)	Short (Caucasian)	6–10	Correct recognition Response latency
Rapid Visual Processing (RVP)	1 Target Tone	7	Response latency Probability of false alarms sensitivity
Paired Associated Learning (PAL)	Recommended Standard Tone	8	number of errors number of trails required memory scores stages completed
One Touch Stocking of Cambridge (OTS)	Short	10	number solved on first choice Mean number of choices to solve Mean latencies
Cambridge Gambling Task (OTS)	Ascending First Shortened Tone	12–18	Risk-taking Decision-making quality Decision time Risk adjustment Delay aversion Impulsivity
Total administration time		49–61	

## Clinical laboratory measures

5

*Anthropometric biomarkers*: Bodyweight will be measured using an electric scale (two decimal accuracies), while the standing height will be measured by a stadiometer at baseline, week 8 and week 14. The body mass index (BMI) will be calculated using these measures.

*Cardiovascular biomarkers*: At each visit, blood pressure will be measured using an Omron HEM7 120 Blood Pressure Monitor. Blood pressure will be measured from the left arm while the participant is seated and at rest. Two readings will be collected for systolic and diastolic blood pressure. Heart rate will likewise be assessed at a resting position using the Omron HEM7 monitor.

*Metabolic biomarkers*: Fasting peripheral blood will be collected in participants at baseline, week 8, and week 14. 0.5 mL of whole blood will be transferred from the EDTA tube to a new tube and frozen until analysis. The remaining samples will be spun at 3000 rpm for 10 min. Serum and Plasma will be transferred to new tubes and frozen at −80 degrees Celsius until analysis. From the samples, the metabolic biomarkers: triglycerides, high-density lipoprotein (HDL-c), low-density lipoprotein (LDL-c), total cholesterol (TC), insulin, glucose, and HbA1c will be measured.

*Immune biomarkers*: Interleukin-6 (IL-6), IL-12, tumor-necrosis-factor (TNF) alpha, albumin, fibrinogen, and c-reactive protein (CRP) will be assessed using the collected blood.

*Neuroendocrine biomarkers*: Dehydroepiandrosterone sulfate (DHEAS) will be assessed from the collected blood samples, while cortisol concentrations will be assessed from hair samples collected at baseline and week 14 using the Salimetrics Saliva Cortisol ELISA kit.

## Randomization

6

For this study, stratified randomization will be used. We will stratify by assuming eight groups based on the following criteria: diagnosis (schizophrenia or bipolar disorder), gender (male or female), and duration of illness (DOI; more or less than 5 years). Groups will be divided as demonstrated in Figure 2.

Each of the stratified groups will be randomly allocated into either KD or AGHE. The allocation will be concealed from the investigators and will only be known by the Clinical Research Coordinator. Each subsequent entry to each stratum will be sequentially followed, thereby creating a stratified, random allocation. Recruitment for this trial will be continuous for 18 months or until the required participation number has been reached.

## Measurement tools used

7

### Wearable devices

7.1

An Oura ring (Ōura, Oulu, Finland) and an Embrace wristband (Empatica, Cambridge, United States) will be offered to all participants to wear for a week during the introductory period before starting the diet (week 1 [T1]) and during week 14, just before finishing the diet. This measurement is optional and can be selectively opted out by the participant. Sensor biomarker data including heart rate (HR), heart rate variability (HRV), and electrodermal activity (EDA) from the Oura and Embrace devices will be utilized to provide an overall autonomic nervous system (ANS) stress score, using a pre-trained machine learning model previously shown to be a reliable predictor of acute stress (61).

### Stool collection

7.2

It will be optional for all participants to supply a stool sample at the start of the trial (prior to T1) and again at the end of the trial period (week 14) for the future analysis of changes in the fecal microbiome composition and its metabolites. The participant will be supplied with a self-collection kit during the Week 0 assessment, and they can collect the specimen at home at their earliest convenience. The kit can be posted to the research team.

### Hair collection

7.3

It will be optional for all participants to supply a hair sample at the start of the trial (prior to T1) and again at the end of the trial period (week 14) for future analysis of cortisol to assess the cumulative impact of the biological stress response over time. The small sample (5 mg) will be taken by a researcher during the physical assessment.

### Glucose and ketone measurement

7.4

Ketone and glucose levels will be monitored by the participants from home. A “blood glucose plus beta-ketone monitoring system” and test strips will be supplied to all participants. The participant will be required to take daily samples by finger prick (1.0 uL blood) 2 h before eating dinner. The monitor system will inform the investigators and the participants about the time spent in ketosis. During the week 0 assessment, participants will be asked a preference to inform us about their daily ketone and glucose results. This may also include a daily reminder text to the participant if they prefer. The participant can choose to either upload a photo of the result to a phone used during the trial, text-message the result to the phone or they can choose to receive a daily phone call and talk to a team member. The trial phone will be monitored by a team member 24/7.

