#### Assessments

2.1.2

Eligible participants progress to the first physical visit (Enrolment Visit at Timepoint 1 [T1]) and are asked to complete a three-day food diary before attending the appointment. During the enrolment visit [T1], formal written consent is obtained by a trial psychiatrist (CL, SG, or OS) before baseline assessments of psychiatric, cognitive, and metabolic outcome measures are taken. Participants are then randomized into either the Ketogenic Diet (KD) or the Australian Guide to Healthy Eating (AGHE) group by stratified, computer-generated blinded allocation. Following randomization, participants progress to the dietitian assessment and group-specific dietary education. Dietary education and counseling for each group are provided by a senior dietitian, including the provision of the existing evidence base for nutrition in mental health to assist in personalizing the KD or AGHE diet. Consideration will be given to their metabolic health, dietary preferences, age, sex, and physical activity level that may impact their estimated energy requirements (EER). Participants will then receive detailed dietary instructions and specific educational material to foster independent meal preparation. All participants, irrespective of their group allocation, will be instructed to complete a 2-week diet “adaptation period” where both groups progressively adjust their diet to minimize any side effects due to metabolic adaptation to the new diet and to allow participants to adjust their daily routine to the new food preparation requirements. Participants will be asked to complete daily food diaries and are provided with weekly dietetic support in the form of face-to-face consultation, and phone-, and email follow-up to increase compliance, alter individual diet prescriptions where required, and for safe cessation of the diet. In the second visit (Mid-Point Visit or Timepoint 2 [T2]), psychiatric and metabolic assessments are repeated. In the third visit (Completion Assessment or Timepoint 3 [T3]), all psychiatric, metabolic, and cognitive assessments are repeated. T1 is at baseline (week 0), T2 occurs on week 8, and T3 on week 14. The intervention is 12 weeks from week 3 to week 14, plus a 2-week washout period, for a total of 14 weeks duration (Figure 1). During the washout period, participants are instructed to progressively revert to a diet of their preference. Participants may also continue with their allocated diet, if they choose to do so.

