Pre-existing psychiatric and metabolic treatment will continue as per the treating team’s medical advice. Metabolic medication might be adjusted for those in the KD group in collaboration with their physician to minimize the risk of hypoglycemia. Participants in both groups will be given a blood ketone and glucose monitoring device at the end of the enrolment visit (T1) and instructed to take a daily capillary blood sample to measure glucose and ketone levels. The measurement will occur consistently every day, 2 h before their routine dinner time. Daily glucose and ketone measurements are uploaded to a team’s database daily and strictly monitored to detect any emergent metabolic abnormality.

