#### Allocation

2.1.3

Participants will be blinded to the study hypothesis and interact with clinicians who are kept blind to their group allocation as far as possible. Allocation will occur only after the initial psychiatrist assessment. If a psychiatrist becomes accidentally unblinded to a participant’s allocation during the running of the trial, a different team psychiatrist will be asked to continue the remaining time points assessment(s) for that participant. Participants in both groups will be treated identically in all respects except for the intervention being tested.

The study is being conducted at a single site at the Translational Research Facility, Australian Institute of Tropical Health and Medicine, James Cook University at Townsville Campus, Queensland, Australia. Human Research Ethics Approval (HREC/2022/QTHS/85408) for this study was received by the Townsville University Hospital HREC board, responsible for the study population’s catchment area.

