
Our trial design has some limitations. Firstly, despite our best efforts to keep the overseeing psychiatrists blind to the dietary arm allocation of individual participants, we cannot rule out the possibility that some participants may disclose their diets during the psychiatric assessments in the middle or at the end of the trial. Also, an argument can be made that some of our motivated participants may have information about the expected benefits of the ketogenic metabolic therapy in their condition, which could conceivably introduce an expectation bias if assigned to the ketogenic arm of the trial. We will, however, obtain their daily blood ketone levels which can be correlated with the results of the psychiatric and cognitive assessment, and give an objective control measure to address the above limitations. Another possible limitation is that due to the nature of this clinical trial conducted in an outpatient setting, relying on the ability of the participant to adhere to a relatively restrictive dietary regime independently, the recruited participants will be better functioning than some other patients with serious mental illness, resulting in a self-selected study population. We acknowledge this limitation, but we argue that although we might be able to demonstrate better adherence in this self-selected group, it may be a strength of the trial to demonstrate symptom improvement in participants who may be somewhat better functioning already. Additionally, demonstrating adherence to a restrictive dietary regimen by a population with severe mental disorders in the community may in itself be regarded as a satisfactory outcome measure.

In conclusion, we expect this randomized controlled clinical trial to assess the feasibility, efficacy, and safety of ketogenic metabolic therapy in schizophrenia and bipolar disorder. To our knowledge, our proposed trial is the first of its kind worldwide. We hypothesize that this study will reveal improvements in symptoms, overall quality of life, and better metabolic functioning for our participants. Results from this trial may inform future studies on more specific mechanisms of action, as well as introduce a novel treatment modality to manage psychiatric disorders that would otherwise have been considered as long-term, debilitating conditions.

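### Ketone readings that largely reveal the arm go to the investigators from whom allocation is concealed, and the Discussion wrongly offers those readings as a control for disclosure and expectation bias

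*Protocol article*

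**What the plan says.** **Who is to be blind.** Section 6 (Randomization): "The allocation will be concealed from the investigators and will only be known by the Clinical Research Coordinator". Section 2.1.3 (Allocation) says that participants will "interact with clinicians who are kept blind to their group allocation as far as possible". If a psychiatrist is unblinded by accident, "a different team psychiatrist will be asked to continue the remaining time points assessment(s) for that participant".

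**Who receives the ketone data.** Section 7.4: "The monitor system will inform the investigators and the participants about the time spent in ketosis". Section 2.1.2 sends the daily readings of both arms to a team "database daily and strictly monitored to detect any emergent metabolic abnormality". Section 7.4 adds that a team member watches the trial phone. Neither section says which staff may not see the readings.

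**Who rates.** Section 2.1.1 describes the principal investigator as a senior psychiatrist, and section 2.1.2 lists the same person among the three trial psychiatrists. Section 2.1.3 implies that team psychiatrists do the assessments at each time point. PANSS and YMRS, both named as primary outcomes in the Abstract, are clinician interviews (sections 3.1 and 3.2).

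**What the ketones are to do.** The Discussion (section 9) concedes two weaknesses: participants may reveal their diet to psychiatrists, and informed participants in the ketogenic arm may expect benefit. It then says that correlating daily ketones with the psychiatric and cognitive results will "give an objective control measure to address the above limitations".

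**The concern.** Sections 6 and 7.4 use the same word, investigators, for those who must not know the arm and for those who are told about ketosis. A rater who knows the arm can shift PANSS and YMRS scores, and nothing in the article keeps the readings from raters.

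The second problem is the remedy. If the Discussion's claim stands, a ketone–outcome correlation found at the end could be read as reassurance against bias, although expectation or rater knowledge alone can produce it. Participants also see their own readings, so expectation can follow ketone level. BDI and WHODAS 2.0 are self-reported primary outcomes.

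**Working it through.** **1. Do the readings reveal the arm?** Section 2.2 says the experimental diet is designed to induce ketosis, and the Discussion uses daily ketones to confirm adherence to it. On the plan's own logic, then, time in ketosis largely identifies the arm.

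The documents give no ketone distributions. As an illustration, *assume* log-normal readings with medians of 1.0 (ketogenic) and 0.2 mmol/L (control) and a log-SD of 0.5.
- Chance that one reading orders a pair correctly: Φ(ln 5 / (0.5·√2)) = Φ(2.28) ≈ 0.99.
- With a cut-off of 0.45 mmol/L: Φ(ln(1.0/0.45)/0.5) = Φ(1.60) ≈ 0.95 of the ketogenic arm and Φ(ln(0.45/0.2)/0.5) = Φ(1.62) ≈ 0.95 of the control arm are classified correctly.

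**2. Does any safeguard cover this?** The replacement rule in section 2.1.3 deals with accidental unblinding of a psychiatrist. A routine feed of readings is not an accident, and no passage separates raters from it.

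**3. Can the correlation act as a control?** Suppose the true arm difference is τ and bias adds b. The expected arm contrast is τ + b. Computing a ketone–outcome correlation changes neither term, so b remains.

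**4. Can bias alone produce the correlation?** The arm size comes from section 8.1, whose figure reproduces. With 75% v 40%, two-sided 5%, 90% power and pooled variance without continuity correction:

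n = [1.960·√(2·0.575·0.425) + 1.282·√(0.75·0.25 + 0.40·0.60)]² / 0.35² = 39.8, so 40 per arm and 80 in total; 80/(1 − 0.20) = 100.

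A simulation then used 40 per arm, 4,000 runs, the ketone distributions above, **no ketone effect**, and a two-sided 5% test of the Pearson correlation. Two assumed inputs vary:
- b, a uniform shift in favour of the ketogenic arm, in SD of the outcome noise.
- g, the effect on ratings (same SD units) per SD of an expectancy trait that correlates 0.7 with log ketones within the ketogenic arm.

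| b | g | Pooled: mean r | Pooled: significant | Ketogenic arm only: mean r | Ketogenic arm only: significant |
|---|---|---|---|---|---|
| 0 | 0 | 0.00 | 5% | 0.00 | 4% |
| 0.3 | 0 | 0.11 | 17% | 0.00 | 5% |
| 0.5 | 0 | 0.18 | 36% | 0.00 | 5% |
| 0.8 | 0 | 0.28 | 70% | 0.00 | 5% |
| 0 | 0.3 | 0.09 | 13% | 0.19 | 22% |
| 0 | 0.5 | 0.15 | 25% | 0.29 | 46% |

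Two hand checks agree.
- *Within arm, on the log scale:* r = 0.7g/√(1 + g²), which gives 0.21/1.044 = 0.20 for g = 0.3 and 0.35/1.118 = 0.31 for g = 0.5. The simulated values are slightly lower because ketones were not log-transformed in the test.
- *Pooled, with a different assumption (arms 3 within-arm SD apart in ketones) and b = 0.5:* r = (3·0.5/4)/√[(1 + 9/4)(1 + 0.25/4)] = 0.375/√(3.25·1.0625) = 0.20. With 80 people this is significant about 44% of the time, against 36% above.

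The rows with g = 0 cut both ways. A uniform bias does not inflate the within-arm correlation, and for the same reason that correlation cannot detect it: b can reach 0.8 SD while the rejection rate stays near 5%.

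**The case against.** Several points on the other side have force.

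- **Rater access is not stated.** A reader might infer that PANSS and YMRS lose their blind by the plan's own data flow. The article does not say so. It speaks of a team database and a team member, and database permissions may sit in the full protocol. What stands is that the wording permits access and that the principal investigator holds both roles.
- **Section 6 may concern only the allocation sequence.** Taken as a lasting blind of all staff it cannot be literal, because the dietitian gives group-specific education (section 2.1.2). This is a fair reading, but it leaves section 6 in need of correction either way.
- **Not every primary outcome is exposed to raters.** It would be wrong to call the clinician ratings the only protected outcomes. CANTAB is delivered digitally with automated data capture (section 4).
- **The evidence given to participants does not reveal the hypothesis.** Section 2.1.3 says "Participants will be blinded to the study hypothesis", and section 2.1.2 describes education "including the provision of the existing evidence base for nutrition in mental health". A reader might see a conflict, but that material goes to both arms, and both arms test ketones daily.
- **The sizes are assumed.** No ketone spread, bias or expectancy loading is in the article. The Abstract predicts the correlation within the intervention group and the Discussion does not say which analysis it means, so the pooled rates may not apply. Within the arm, only expectancy that varies with adherence creates the artefact.
- **The limitation is admitted, and the claim is one sentence in the Discussion.** True. The fault lies in the remedy offered for the limitation.

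**Conclusion.** The point holds in two parts.

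First, sections 6 and 7.4 conflict as written, and the article leaves the blinding of the clinician-rated primary outcomes unprotected against a routine feed of readings. It does not show that raters look at them.

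Second, the claim of an objective control is wrong. Ketones arise after randomisation from allocation and adherence, and correlating them with outcomes does not correct the randomised contrast. This part needs no assumed number.

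How often bias alone would yield a significant correlation does rest on assumptions: roughly 17–70% pooled for a bias of 0.3–0.8 SD; roughly 22–46% within the ketogenic arm for the expectancy loadings used; about 5% there if the bias is uniform. It would go too far to say that ketone data carry no information. They show exposure and adherence, and a within-arm correlation is not inflated by a uniform bias.

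**What to change.** 1. In sections 7.4 and 2.1.2, name the recipients of ketone readings (device feed, trial phone, database) as existing unblinded staff who do not rate outcomes. Leave the safety monitoring itself in place.
2. State that rating psychiatrists have no access to a participant's readings until that participant's T3 ratings are complete. If safety requires a psychiatrist to see one earlier, let the replacement rule in section 2.1.3 apply, worded to cover more than accidents.
3. Reconcile section 6 with section 7.4 and with the dietitian's necessary knowledge of the arm.
4. Withdraw the Discussion's claim of an objective control, and label ketone–outcome correlations exploratory and non-randomised.

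The cost is some work on access permissions, a check that non-rating staff can cover the monitoring, and a weaker mechanistic claim. Design, sample size and treatment do not change. An expectancy rating before randomisation and arm-guess questions at T3 would address the admitted bias more directly, but they are optional.

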**Outcomes:**

The primary outcomes include psychiatric and cognitive measures, reported as symptom improvement and functional changes in the Positive and Negative Symptoms Scale (PANSS), Young Mania Rating Scale (YMS), Beck Depression Inventory (BDI), WHO Disability Schedule, Affect Lability Scale and the Cambridge Cognitive Battery. The secondary metabolic outcomes include changes in body weight, blood pressure, liver and kidney function tests, lipid profiles, and markers of insulin resistance. Ketone and glucose levels will be used to study the correlation between primary and secondary outcomes. Optional hair cortisol analysis will assess long-term stress and variations in fecal microbiome composition. Autonomic nervous system activity will be measured via wearable devices (OURA ring and EMBRACE wristband) in the form of skin conductance, oximetry, continuous pulse monitoring, respiratory rate, movement tracking, and sleep quality. Based on the encouraging results from established preclinical research, clinical data from other neurodevelopment disorders, and open trials in bipolar disorder and schizophrenia, we predict that the ketogenic metabolic therapy will be well tolerated and result in improved psychiatric and metabolic outcomes as well as global measures of social and community functioning. We additionally predict that a correlation may exist between the level of ketosis achieved and the metabolic, cognitive, and psychiatric outcomes in the intervention group.

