In case of demonstrated efficacy, it is crucial to understand the mechanism of action of this novel metabolic intervention to give informed advice to the psychiatric community on any potential change in clinical practice. Our trial will collect data from different domains, including systemic metabolism and inflammatory processes, autonomic nervous system activity, sleep patterns, and changes in the gut microbiome. Outcome measures from these systems, when correlated with improved psychiatric symptoms, cognitive functions, and overall daily functioning will inform us about the potential involvement of underlying mechanisms. With regards to mechanisms of action of dietary intervention, the possible mediating role of the gut microbiome is of primary importance as the ecosystem of the bacteria in the gastrointestinal system interacts with the consumed diet even before the different nutrients and other food-derived molecules get into the bloodstream (64–67). It is conceivable that some of the effects of the ketogenic metabolic therapy may be mediated by the gut microbiome, either directly through microbiome-derived metabolites that reach the brain or indirectly through changes in the enteric nervous system activity. We aim to establish such a role for the gut microbiome by demonstrating ketogenic diet-related changes associated with symptom improvement. Ketone bodies, beta-hydroxybutyrate, and acetoacetate are the metabolic products of the liver while on the ketogenic diet (36). Ketones have been shown to directly benefit brain bioenergetics (68, 69). The daily ketone monitoring will make it possible not only to confirm adherence to the ketogenic diet but also to correlate ketone levels with daily changes in the self-reported energy levels of the participants. Alterations in autonomic nervous system activity and sleep have been widely reported in schizophrenia (70) and bipolar disorders (71, 72). The ketogenic diet seems to be effective in influencing these functions. Therefore, the potential mechanistically important role of autonomic nervous system activity and sleep health can be uncovered by monitoring these functions using wearable devices before the introduction and at the end of the dietary intervention. Although human studies are rarely designed to include an experimental intervention that directly informs about exact mechanisms of action, the complex analysis of multiple, interacting systems will show biomarkers that are specifically modified by the treatment and associated with improvements in different symptom domains.

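### Ketone values sent by text or phone are unverified, and one reading a day gives levels rather than time in ketosis, so the claims of confirmed adherence and objective control go too far

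*Protocol article*

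**What the plan says.** The schedule is stated twice and agrees. Section 7.4: "The participant will be required to take daily samples by finger prick (1.0 uL blood) 2 h before eating dinner". Section 2.1.2: "The measurement will occur consistently every day, 2 h before their routine dinner time".

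Section 7.4 offers three reporting routes, at the participant's choice. The first is an image: "The participant can choose to either upload a photo of the result to a phone used during the trial". The other two are to "text-message the result to the phone or they can choose to receive a daily phone call and talk to a team member". Section 2.1.2 adds that the values reach a team database each day and are watched for metabolic abnormalities.

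The article makes four claims or uses of these data:

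- Duration (section 7.4): "The monitor system will inform the investigators and the participants about the time spent in ketosis".
- Adherence (Discussion): "The daily ketone monitoring will make it possible not only to confirm adherence to the ketogenic diet".
- Dose-response (Abstract, Outcomes): "a correlation may exist between the level of ketosis achieved and the metabolic, cognitive, and psychiatric outcomes in the intervention group".
- Bias control (Discussion, limitations): correlating ketone levels with the psychiatric and cognitive results is to "give an objective control measure to address the above limitations". Those limitations are possible unblinding of the psychiatrists and participants' expectations of benefit.

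Section 2.1.2 also plans daily food diaries and weekly dietetic support.

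**The concern.** With two of the three routes, the trial receives a number that the participant typed or spoke. Participants know which diet they were taught, and the Discussion concedes that some may expect benefit from the ketogenic diet. A value relayed by such a participant is not independent of the expectation it is meant to control for. Days off the diet are also the easiest to leave unreported.

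Separately, a reading at one fixed point in the day says nothing about the other hours, so it cannot yield a duration.

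At stake are how adherence is described, how well the ketone–outcome correlation can be estimated, and whether the Discussion's answer to unblinding and expectation bias stands.

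**Working it through.** **The plan's own design figure.** Section 8.1 gives 75% v 40% response, two-sided 5%, 90% power and 1:1 allocation. With pooled variance under the null and mean proportion 0.575:

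n per arm = [1.960·√(2×0.575×0.425) + 1.282·√(0.75×0.25 + 0.40×0.60)]² / 0.35² = (1.370 + 0.838)² / 0.1225 ≈ 39.8, so 40 per arm and 80 in total. Then 80/0.80 = 100. Power at 40 per arm is 0.901. The figure reproduces and uses no ketone data.

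**Number of readings.** From T1 to T3: 14 × 7 = 98 (8 × 7 = 56 to T2, then 6 × 7 = 42 to T3). Without the two adaptation weeks: 12 × 7 = 84. All are taken at the same point in the day. They support a mean level, or the share of days with a ketotic pre-dinner reading, but not hours in ketosis.

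**Device evidence by route.** A photo shows the meter display. A text or a phone call does not. The daily database entry in section 2.1.2 does not change this, because the only routes described in section 7.4 go through the participant.

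**Any other ketone source?** The blood panel in section 5 lists lipids, insulin, glucose and HbA1c, but no ketone. The home readings are the only ketone data described. The food diaries are also self-report and cannot verify them.

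**Illustration 1: selective non-reporting (assumed rates).** Let true ketosis be 60% of days, all ketotic days be reported, and a fraction u of non-ketotic days go unreported. Share among reported days = 0.60 / [0.60 + 0.40(1 − u)].

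- u = 0.10: 0.60/0.96 = 62.5%.
- u = 0.40: 0.60/0.84 = 71.4%.

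The overstatement is 2.5 to 11.4 percentage points. It can arise by any route, since a photo can also be left unsent.

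**Illustration 2: missing days counted as non-ketotic.** With the same 60% and 20% of readings missing at random (assumption), the share of all scheduled days is 0.60 × 0.80 = 48%, which is 12 points too low. Neither denominator is safe alone.

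**Illustration 3: random error and the correlation.** Assume 50 × 0.80 = 40 ketogenic-arm completers. Observed r = true r × √reliability; power = Φ[atanh(observed r)·√37 − 1.96]. True r and reliability are assumptions.

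| Reliability | Observed r (true 0.5) | Power | Observed r (true 0.3) | Power |
|---|---|---|---|---|
| 1.0 | 0.50 | 92% | 0.30 | 47% |
| 0.8 | 0.45 | 83% | 0.27 | 39% |
| 0.6 | 0.39 | 70% | 0.23 | 30% |
| 0.4 | 0.32 | 51% | 0.19 | 21% |

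This covers random error only. Selective or favourable reporting could bias the correlation in either direction.

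**The case against.** Four points can fairly be made for the plan.

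- *Adherence is measured.* A daily blood ketone value is a usable day-level marker, and diaries and weekly dietitian contact add to it. This stands. A reader might infer that adherence goes unmeasured; the article does not support that. The fault is limited to the strength of *confirm* for unverified values.
- *Duration is not the planned exposure.* The phrase on time in ketosis appears once, as information fed back to investigators and participants. The planned correlations in the Abstract and Discussion refer to levels, which daily readings do give. This also stands, so the phrase is a wrong description and not a wrong analysis.
- *The missing check is partly inferred.* The article neither describes nor rules out reading the meter at visits, and a condensed article may leave source-data checks to the full protocol. This stands in part. One cannot say that no verification exists. But the article itself sets out the routes and makes the claims, and it does not restrict the claims to verified values.
- *Efficacy is untouched.* Section 8.2 compares the arms as randomised under intention to treat. This stands: a reader might think the main comparison is compromised, but it does not use ketone values.

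**Conclusion.** The point holds as an overclaim with a cheap remedy. For values sent by text or phone, *confirm* and *objective* are not supported by the procedure described. For all values, one reading a day at a fixed hour does not give time in ketosis.

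The size is uncertain. Under the assumed 10–40% selective non-reporting, a true 60% appears as 62.5–71.4%. Under assumed reliability of 0.6 and a true correlation of 0.5, power for the correlation falls from 92% to 70%. The article gives no reporting rate, reliability or ketone cut-off, so these figures show what is possible and are not estimates for this trial.

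The effect is confined to the adherence description, the ketone–outcome correlation and the stated bias safeguard. The sample size and the randomised comparison are unaffected.

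**What to change.** 1. Keep the daily messages for safety monitoring, by whichever route the participant prefers.
2. At the existing T2 and T3 visits, download or photograph the meter's stored dated readings, and use these verified values for the adherence and correlation analyses. This assumes the meter stores dated readings, which the article does not say. If it does not, encourage the photo route and flag each value by the route it came by.
3. Replace the time-in-ketosis wording with the proportion of pre-dinner readings at or above a ketone cut-off fixed before analysis; the article states none. Report it both among days with a reading and among all scheduled days, with missing days shown separately. In the illustrations above, the first figure is too high under selective non-reporting and the second too low under random missingness, so both are needed.
4. Limit *confirm* and *objective* in the Discussion to device-verified values.

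The cost is a few minutes per participant at two visits already scheduled, plus a short definition. The adherence figure may come out less favourable. A download recovers readings taken but not sent; it cannot recover readings never taken, which is why missing days must stay visible.
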